##### Other variables

- Psychiatric diagnosis: This will be performed with the MINI psychiatric interview [37], a psychiatric interview developed by our group and extensively used for the study of psychiatric disorders in primary care. It allows the use of DSM-IV diagnostic criteria. We specifically assess the presence of Post-traumatic Stress Disorders because it seems to be associated with a worse prognosis [38].

- Hospital Anxiety Depression Scale (HADS): This is a self-reported scale designed to screen for the presence of depression and anxiety disorders in medically ill patients. It contains 14 items rated on four-point Likert-type scales. Two subscales assess depression and anxiety independently (HADS-Dep and HADS-Anx, respectively) [39]. Patients with 14 or more points in the complete scale (or more than eight in either of the two subscales) are considered "probable cases" of anxiety and/or depression. The validated Spanish version of this questionnaire will be used [40].

### Procedure

Patients diagnosed with FM will be recruited by GPs from the selected health centres to fill the required sample. At baseline, trained researchers will administer questionnaires to assess socio-demographic, main outcome and other variables, and pain-related psychological constructs. At one-year follow-up, other researchers who will be blind to the results at baseline will administer the main outcome variables to the same patients.

### Statistical methods

#### Sample size

To calculate the sample size, it is necessary to know the population that suffers from FM in the region of Aragon. According to epidemiological studies [2] the prevalence of FM in Spain is 2-3%. The population of Aragon is calculated at 1,250,000 inhabitants, and based on this prevalence data the number of persons diagnosed with FM could be 30,000 patients. With a confidence level of 95%, an estimated error of 5% and considering the most unfavourable assumption (*p *= 0.5), a sample of 305 patients will be necessary, using an accuracy of 3%. EPIDAT 3.1 was used to calculate the sample size.

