- *Mindfulness: *This concept is defined as the practice of being mindful, focused on the present moment and without judging the situation we have to live through [20]. It has been demonstrated that mindfulness correlates positively with several measures of psychological well-being and that it is associated with significant long-term improvement in patients with pain and, specifically, in FM [20,21].

- *Positive and negative affect: *Affect has been described as the observable expression of emotion, which can be both positive and negative [22,23]. Negative affect has been related with poor outcomes in FM [22,23], but recently the emphasis has been put on the affect balance style (relative levels of negative and positive affect) as a prognostic marker in FM [24].

It is not currently known whether these psychological constructs correlate between themselves or even overlap each other. In addition, their specific significance for prognosis and treatment on chronic pain disorders has not been assessed. The general aim of this study is to assess the importance of pain-related psychological constructs on function and pain in patients with FM. The specific objective is to assess correlations and possible overlapping among constructs.

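### The 305 patients are justified as a sample for estimating one proportion, which no aim or analysis targets, and 305 does not follow from the inputs given

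*Protocol article*

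**What the plan says.** The Sample size section starts from the premise "To calculate the sample size, it is necessary to know the population that suffers from FM in the region of Aragon". It takes a prevalence of 2-3% and 1,250,000 inhabitants, and concludes that "the number of persons diagnosed with FM could be 30,000 patients". To this it adds a 95% confidence level, "an estimated error of 5% and considering the most unfavourable assumption" (p = 0.5), and the result: "a sample of 305 patients will be necessary, using an accuracy of 3" per cent. The software is named. No power, effect size or outcome rate enters.

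The Background section sets the target: "The general aim of this study is to assess the importance of pain-related psychological constructs on function and pain in patients with FM". That section also names a narrower objective, namely the correlation and overlap among the constructs.

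The Analysis strategy section plans descriptive statistics, group comparisons, a Spearman correlation matrix, a cluster analysis, and a logistic regression of the one-year outcomes on the constructs with adjustment for socio-demographic and clinical variables.

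According to Table 1 the constructs are measured at baseline only. The main outcomes are measured again at one year, when, in the words of the Procedure section, "other researchers who will be blind to the results at baseline will administer the main outcome variables to the same patients". The Setting and study sample and Procedure sections describe recruitment as continuing until the required sample is reached, so 305 is a number recruited.

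**The concern.** A sample-size section should tell the reader what the planned number can estimate or detect for the study's own questions. This one gives the precision of a single percentage at a single time point, and no planned analysis has a population percentage as its target. A reader cannot learn from it how precisely the correlations among constructs will be estimated, or how strong a predictor must be for the one-year model to find it.

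Two further features add to this. The section states two precision figures, 5% and 3%, next to one sample size, and they cannot both describe it. And the number called necessary is fixed at recruitment, whereas the predictive analysis uses only patients seen again a year later.

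At stake is the credibility of the stated justification and the reader's ability to judge the study's sensitivity. The validity of the estimates themselves is not in question.

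**Working it through.** **1. The plan's own figure.** Inputs from the Sample size section: N = 30,000, p = 0.5, 95% confidence (two-sided z = 1.96; the sides are not stated), and d = 0.05 or 0.03 read as an absolute half-width. For one proportion in a finite population:

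n = N z² p(1−p) / [d²(N−1) + z² p(1−p)], with z² p(1−p) = 3.8415 × 0.25 = 0.9604.

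- d = 0.05: 28,811 / (74.998 + 0.960) = 379.3, so 380.
- d = 0.03: 28,811 / (26.999 + 0.960) = 1,030.5, so 1,031.

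Neither gives 305. Other readings do not either:

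| Reading (N = 30,000, p = 0.5) | d = 5% | d = 3% |
|---|---|---|
| 95% two-sided | 380 | 1,031 |
| 95% one-sided, or 90% two-sided | 269 | 734 |
| 97% two-sided | 464 | 1,254 |

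In reverse, with n = 305: half-width = 1.96 × √(0.25/305) = 0.056, or 5.6 points, and the finite-population correction does not change this to one decimal. To match 5%, the confidence level would have to be about 92%, or p about 0.28. To match 3%, it would have to be about 71%, or p about 0.08. The section states none of these.

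**2. Is the population size needed?** With d = 0.05 and 95% two-sided, the formula gives 378.3 at N = 25,000 (2% of 1,250,000), 380.3 at N = 37,500 (3%) and 384.1 with no finite limit. Even for a proportion the regional count hardly matters. It does not enter the usual calculations for correlations or regression coefficients at all.

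**3. What 305 delivers at baseline.** Fisher z with the variance factor 1.06 for Spearman:

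- 95% half-width, largest at a correlation of zero: tanh(1.96 × √(1.06/302)) = 0.116.
- Correlation detectable with 80% power, two-sided 5%: tanh((1.960 + 0.842) × √(1.06/302)) = 0.164.

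The constructs are measured only at baseline, so one-year loss does not change these figures.

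**4. What 305 delivers at one year.** The planned model is logistic, so the natural scale is an odds ratio per SD of a construct. With outcome rate P and squared multiple correlation R² between the construct and the other covariates:

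OR = exp{ (1.960 + 0.842) / √[n P(1−P)(1−R²)] }.

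The article gives no outcome rate, R² or loss rate. All three are assumptions here: P from 0.3 to 0.5, R² from 0 to 0.5, loss of 0%, 20% or 30%.

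| Assumed loss | n analysed | P = 0.5, R² = 0 | P = 0.3, R² = 0.5 |
|---|---|---|---|
| 0% | 305 | 1.38 | 1.64 |
| 20% | 305 × 0.8 = 244 | 1.43 | 1.74 |
| 30% | 305 × 0.7 = 213.5, about 214 | 1.47 | 1.81 |

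For example, at n = 244, P = 0.5 and R² = 0: 2.802 / √61 = 0.359, and exp(0.359) = 1.43.

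**The case against.** The strongest reply is that nothing in the study has to change. The number stays, the analyses stay, and 305 patients give usefully precise correlations. A null result for a construct can still be read from its estimate and confidence interval, whatever argument was used beforehand to choose the number. That stands. A reader might infer that null findings would be uninterpretable, or that the sample is inadequate; the documents support neither inference.

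A second reply is that a finite-population formula does take N as an input, so the opening premise merely describes the chosen method. That is fair as a description, but the method does not fit the aims, and N barely moves its result.

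A third reply concerns loss. A condensed article may leave the expected loss rate to the full protocol, so the absence of a rate is not in itself a fault. It is also tempting to say that loss undermines the whole study. It does not: the correlation matrix and the clusters use baseline data only, and even for the one-year model an assumed 30% loss moves the detectable odds ratio only from 1.38-1.64 to 1.47-1.81. What remains is narrower: the number called necessary is the number recruited, and the one-year model will use fewer after any loss.

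The core of the point does not depend on anything left to another document. The section sets out a complete calculation, with inputs, result and software. The calculation addresses the wrong quantity, and its result does not follow from its inputs.

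**Conclusion.** The point holds in this form. The justification of 305 rests on the precision of a single proportion, which is not the target of any stated aim or planned analysis. On its own terms it also fails: under the stated confidence level, p and population, 5% requires 380 and 3% requires 1,031, against a true half-width of about 5.6 points at 305. This assumes that both percentages are absolute half-widths; no alternative reading in the working gives 305.

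The finding does not show that 305 is too few. For the baseline correlations the sample is informative (half-width at most about 0.12, detectable correlation about 0.16). For the one-year logistic model the detectable odds ratio per SD lies between 1.38 and 1.81 across the assumed outcome rates, covariate R² and losses of 0-30%. Whether that is sensitive enough is for the sponsor to argue; the present text gives no basis for the argument.

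**What to change.** Keep 305. In the Sample size section:

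- Remove the 5% and 3% precision figures and the statement that the size of the Aragon FM population is needed.
- For the specific objective, state that 305 patients give a 95% half-width of at most about 0.12 for a Spearman correlation, and 80% power at two-sided 5% for a correlation of about 0.16.
- For the one-year logistic model, state the assumed loss, outcome rate and R² with covariates, label them as assumptions, and give the resulting detectable odds ratio per SD. With outcome rates of 0.3-0.5 and R² of 0-0.5 this is about 1.38-1.64 at n = 305, 1.43-1.74 at n = 244 (20% loss) and 1.47-1.81 at n = 214 (30% loss).
- Say that 305 is the number recruited and that loss affects the one-year model only.

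The cost is a rewritten paragraph, with no extra patients and no change to the analyses. The price is that the stated justification will look less favourable than a 3% accuracy, but it will describe the study that is planned.

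### The sample size of 305 does not follow from the inputs printed beside it, and the text does not say whether 5% or 3% is the margin

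*Protocol article*

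**What the plan says.** The protocol article justifies the study size in one place, the Sample size section under Statistical methods. It builds up a finite population: "The population of Aragon is calculated at 1,250,000 inhabitants", "the prevalence of FM in Spain is 2-3" per cent, and from these "the number of persons diagnosed with FM could be 30,000 patients".

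It then lists the settings, "With a confidence level of 95%, an estimated error of 5% and considering the most unfavourable assumption" (given as p = 0.5), and concludes that "a sample of 305 patients will be necessary, using an accuracy of 3" per cent. EPIDAT 3.1 is named as the software. The section does not say how the 5% and the 3% relate, and gives no power, effect size, dropout allowance or design effect.

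The figure is operative: under Setting and study sample, general practitioners enrol eligible patients until the required number is reached.

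**The concern.** Everything the standard formula needs is printed next to its result, so the result can be checked. A margin of 5 points and a margin of 3 points at p = 0.5 lead to very different sample sizes, and 305 lies below both. Two percentages appear in one sentence under different names (error and accuracy), and a reader cannot tell which of them the study was sized for.

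At stake is the only stated reason for recruiting 305 patients. Someone relying on the section would believe that 305 secures a precision of 3 or 5 points, and it secures neither.

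**Working it through.** **Inputs, all from the Sample size section**
- Confidence 95%, taken as two-sided, so z = 1.96. Sidedness is not stated; two-sided is the convention for a confidence interval.
- p = 0.5, so p(1 − p) = 0.25.
- N = 30,000.
- Candidate margins d = 0.05 and d = 0.03.
- Stated result: n = 305.

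**Formula**
- Without finite-population correction: n0 = z² p(1 − p) / d².
- With it: n = n0 / (1 + (n0 − 1)/N), rounded up.

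**Attempt to reproduce 305**
- d = 0.05: n0 = 3.8415 × 0.25 / 0.0025 = 384.15; n = 384.15 / (1 + 383.15/30,000) = 379.3, so **380**. Without the correction, 385.
- d = 0.03: n0 = 3.8415 × 0.25 / 0.0009 = 1,067.07; n = 1,067.07 / (1 + 1,066.07/30,000) = 1,030.5, so **1,031**. Without the correction, 1,068.
- 305 is not reproduced: 380/305 = 1.25 and 1,031/305 = 3.38.

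**Variants that might rescue it**
- Population count: 2% and 3% of 1,250,000 are 25,000 and 37,500 (30,000 is 2.4%). Over that range the requirement is 379 to 381 at 5 points and 1,024 to 1,038 at 3 points.
- One-sided 95% (same as two-sided 90%): 269 and 734.
- Continuity-corrected: 399 and 1,062.

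**What 305 delivers at p = 0.5**
- Half-width: 1.96 × √(0.25/305) = 0.0561, or 5.61 points. The finite-population factor √((30,000 − 305)/29,999) = 0.995 brings it to 5.58 points.
- Against 3 points: 5.58/3 = 1.86 times too wide. Against 5 points: 0.58 points too wide.
- Standard error √(0.25/305) = 0.02863. For ±5 points, z = 0.05/0.02863 = 1.75, or about 92% confidence. For ±3 points, z = 0.03/0.02863 = 1.05, or about 71%. (Both without the finite-population correction.)

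**What would have to change to obtain 305**
- In p: n = 305 with N = 30,000 corresponds to n0 = 305 × 29,999/29,695 = 308.1. At 5 points p(1 − p) = 308.1 × 0.0025/3.8415 = 0.2005, so p ≈ 0.28. At 3 points p(1 − p) = 308.1 × 0.0009/3.8415 = 0.0722, so p ≈ 0.08. Both contradict p = 0.5.
- In N: N = 305 (n0 − 1)/(n0 − 305) gives about 1,477 at 5 points and 427 at 3 points. Both contradict 30,000.

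**Effect of losses by one year.** The section states no dropout rate, so 10% and 20% are assumptions. They leave about 275 and 244 patients, with half-widths of 0.98/√275 = 5.9 and 0.98/√244 = 6.3 points.

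**The case against.** The strongest objection concerns the two percentages. A reader might infer that the sentence sets two incompatible margins. The document does not establish that. The phrase "With a confidence level of 95%, an estimated error of 5" per cent can be read as naming a confidence level and its complementary error rate, which leaves 3% as the only margin and removes the conflict. That 305 fails at 3% cannot rule this reading out, because 305 also fails at 5%; the arithmetic does not reveal which meaning was intended. This part of the objection stands in full. What remains is that the text does not identify the margin, and that 305 follows on neither reading.

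A second inference to resist is that the planned analyses are therefore too small. The aims are the importance of the constructs for function and pain, and the correlation and overlap among them. The Analysis strategy section plans group comparisons, logistic regression, Spearman correlations and cluster analysis. None targets a single population proportion, and nothing here shows that any of them is compromised at 305. The defect lies in the stated justification.

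It can also be said that an article condenses a fuller protocol. That excuses omissions, but here the inputs and the result are printed together and disagree. If the EPIDAT run used other inputs, the printed ones are wrong.

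Finally, dropout might be thought to explain 305. An allowance would raise 380, not lower it. The nearest approaches need unstated steps: 380 × 0.8 = 304 requires an unexplained 20% reduction, and a one-sided calculation with an assumed 10% dropout gives about 301.

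**Conclusion.** The point holds. With 95% confidence, p = 0.5 and N of about 30,000, a 5-point margin needs 380 patients and a 3-point margin needs 1,031. The document's own prevalence range moves these by only a few patients. The stated 305 meets neither; its half-width is about 5.6 points.

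The conclusion rests on a two-sided interval and the usual single-proportion formula; the one-sided and continuity-corrected forms do not give 305 either. The 5.6 points is a best case: it assumes simple random sampling and all 305 patients analysed, whereas patients are enrolled by general practitioners across centres and outcomes are measured again after one year. The documents cannot show whether the slip lies in the margin, in p, in N or in the result. The section needs correcting, but this is not evidence that the study's main analyses will fail.

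**What to change.** First retrieve the inputs of the EPIDAT run. If they differ from those printed, print the true ones and say which percentage is the margin.

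If they do not differ, keep 305, delete the clause claiming 3% accuracy and any implication of a 5% margin, and state what the number gives. Suggested wording:

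*305 patients give a two-sided 95% confidence half-width of about 5.6 percentage points for a proportion of 0.5, at baseline, assuming simple random sampling; with losses by one year it will be wider.*

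The cost is a sentence of protocol text and a check of the software run. No patients are added. The downside is that the stated precision becomes less favourable than the section now suggests.

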#### Analysis strategy

At baseline, means and standard deviations will be calculated for continuous variables in the study in case of normality, or medians and interquartile periods where this hypothesis is not fulfilled. The Kolmogorov-Smirnov test will be applied to ensure the adjustment of data to a normal distribution.

The existence of differences in socio-demographic, main outcome and other variables regarding pain-related psychological constructs will be analysed. These differences will be studied using Chi Square test for qualitative variables, with the Fisher test being utilized when necessary. To determine the relationship between categorical variables with one or two levels and quantitative variables, Student T test or variance analysis will be used, respectively, for variables fulfilling the normality hypothesis. For the remaining variables, non-parametric tests such as Man-Whitney U or Kruskall-Wallis will be used. To assess the predictive value of pain-related psychological construct on main outcome variables at one-year follow-up, use will be made of a logistic regression analysis adjusted for socio-demographic and clinical variables.

A Spearman Rho non-parametric correlation matrix will be developed to determine the relationship between pain-related psychological constructs and possible overlapping, including these constructs and the other variables, for the analysis of the significance of this matrix and each one of the calculated correlations. Patients will be grouped according to pain-related psychological constructs using cluster analysis, with a profile graph to represent the results of this multivariant analysis. Data will be analysed using the SPSS 15 statistical package.

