## Methods/Design

### Design

Multicentric, naturalistic, one-year follow-up study.

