### Measurements

The variables and instruments of measurement are summarized in Table 1.

**Table 1 T1:** Study variables

Instrument	Assessment area	Time(s) of assessments	Applied by
Sociodemographic data form assistant	Sex, age, marital status, educational level, occupation, income	Baseline	Research

Clinical variables	Family & personal medical & psychiatric history, length of the disorder, main symptoms, psychiatric comorbidity	Baseline	Research

SPPI psychiatric interview [37]	Psychiatric diagnosis	Baseline	Psychiatrist
Pain catastrophizing scale [31]	Severity of catastrophizing	Baseline	Research

Pain acceptance scale [32]	Acceptation of pain	Baseline	Research

Pain Self-Perception Scale (PSPS) [33]	Mental defeat	Baseline	Research

Psychological Inflexibility in Pain Scale (PIPS) [34]	Pain psychological inflexibility	Baseline	Research

Injustice Experience Questionnaire (IEQ) [19]	Perceived injustice	Baseline	Research

Mindful Attention Awareness Scale (MAAS) [21]	Mindfulness	Baseline	Research

Positive & Negative Affect (PANAS) [36]	Positive and Negative Affect	Baseline	Research

Hospital Anxiety Depression Scale (HADS) [40]	Anxiety, depression	Baseline	Research

Fibromyalgia Impact Questionnaire [26]	General function	Baseline and follow-up	Research

Pain Visual Analogue Scale (PVAS) [29]	Pain	Baseline and follow-up	Research

Pain assessed by sphygmomanometer [30]	Pain	Baseline and follow-up	Research

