#### Secondary variables

##### Socio-demographic variables

The following socio-demographic data will be collected: sex, age, marital status (single, married/relationship, separated/divorced, and widowed), educational level (no studies, primary, lower secondary, upper secondary, and university), occupation and income. In addition, relevant clinical variables (family and personal medical and psychiatric history, length of the disorder, main symptoms and medical comorbidity) will be also assessed.

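### The one-year prognostic model does not name the baseline value of the outcome as a covariate, so a construct that only tracks baseline severity may be declared a predictor

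*Protocol article*

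**What the plan says.** The Background section gives the aim: "The general aim of this study is to assess the importance of pain-related psychological constructs on function and pain in patients with FM". The design is a "Multicentric, naturalistic, one-year follow-up study".

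For the one-year question, the Analysis strategy section gives a purpose and a model. The purpose is "To assess the predictive value of pain-related psychological construct on main outcome variables at one-year follow-up"; for this, "use will be made of a logistic regression analysis adjusted for socio-demographic and clinical variables".

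Clinical variables are defined under Socio-demographic variables: "relevant clinical variables (family and personal medical and psychiatric history, length of the disorder, main symptoms and medical comorbidity". The clinical row of Table 1 is nearly the same, with psychiatric in place of medical comorbidity.

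FIQ, PVAS and sphygmomanometer pain threshold appear under a separate heading, Main outcome variables. Table 1 times all three as "Baseline and follow-up". The Procedure section keeps the classes apart: "At baseline, trained researchers will administer questionnaires to assess socio-demographic, main outcome and other variables, and pain-related psychological constructs".

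Nowhere does the article adjust a one-year analysis for the baseline outcome or analyse change from baseline. Baseline outcomes serve only the cross-sectional comparisons and, possibly, the Spearman matrix.

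**The concern.** Constructs and outcomes are measured at the same baseline assessment, and the Background itself associates catastrophizing with more intense pain and acceptance with less pain. Outcome scores at one year can be expected to depend partly on where the patient started. If the baseline score is not in the model, the construct coefficient mixes two things: how ill the patient already was, and how the patient fared from there.

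The Background names the constructs' significance for prognosis as the knowledge gap, and it values acceptance for being related to adaptation independently of pain severity. The model as described cannot show such independence. A construct could be presented as a prognostic factor when it carries no information about the course beyond the baseline FIQ or pain score.

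**Working it through.** **Inputs from the article.** Logistic regression and its adjustment set (Analysis strategy); definition of clinical variables (Socio-demographic variables, Table 1); outcomes measured at both times (Table 1); n = 305 (Sample size: "a sample of 305 patients will be necessary, using an accuracy of 3"%). The article has no figure of its own on this point to reproduce. The 305 only supplies n. It does not follow from the stated precision inputs (with p = 0.5 and a population of 30,000, about 379 at 5% and 1,030 at 3%), but that is a separate matter and 305 is taken as planned.

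**Inputs assumed, because the article gives none.** r = correlation of construct with baseline outcome; rho = correlation of baseline with one-year outcome; outcome split at the median; two-sided 5% Wald test. The construct has no effect on the one-year outcome once baseline is known.

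**Step 1, by hand.** Under these assumptions the construct still correlates with the continuous one-year outcome by r × rho. A median split multiplies this by √(2/π) = 0.798. The approximate test statistic without baseline is z = 0.798 × r × rho × √305, with √305 = 17.46, and the rejection rate is about P(Z > 1.96 − z).

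- (0.2, 0.4): 0.798 × 0.08 × 17.46 = 1.11; P(Z > 0.85) ≈ 20%
- (0.3, 0.5): 0.798 × 0.15 × 17.46 = 2.09; P(Z > −0.13) ≈ 55%
- (0.5, 0.6): 0.798 × 0.30 × 17.46 = 4.18; P(Z > −2.22) ≈ 99%

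**Step 2, by simulation.** Logistic regression throughout, so that only the covariate changes; at least 1,500 runs per setting. The table shows how often the construct is declared a predictor.

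| Model | (0.2, 0.4) | (0.3, 0.5) | (0.5, 0.6) |
|---|---|---|---|
| No baseline outcome, n = 305 | 20% | 55% | 99% |
| Same, plus a symptom proxy correlated 0.5 with baseline | 14% | not run | 92% |
| No baseline outcome, 30/70 split | 18% | not run | 98% |
| No baseline outcome, 244 completers (assumed 20% loss) | 15% | 47% | 97% |
| With baseline outcome, n = 305 | about 5% | about 5% | about 5% |

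With r = 0, the rate without baseline stays near 5%.

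**Step 3, imperfect baseline measurement.** If the baseline score has reliability 0.75 (assumed) and the construct tracks true severity, the adjusted model rejects in about 6% at the weakest pair and 22% to 25% at the strongest. If the assumed correlations are those of the measured scores, so that the true ones are stronger, the rate at the strongest pair is about 45%.

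**Step 4, precision.** Adding baseline raises the construct's standard error in the logistic model by about 7% to 22% across these pairs.

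**The case against.** The strongest reply is that a journal article names covariates by category and leaves the list to a fuller plan, so nothing rules baseline outcomes out. The Background calls pain the most common and disabling symptom, so main symptoms could include baseline pain. This has some force for PVAS and less for FIQ and pain threshold. It does not dispose of the point: the article fixes the adjustment classes, keeps the main outcomes in another class throughout, and a partial symptom proxy leaves most of the inflation in place.

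Second, the question asked is partly a choice. If catastrophizing or acceptance shaped severity before enrolment, conditioning on baseline removes part of that contribution, and total prediction is a legitimate target. That stands, and is a reason to report both models. The term predictive value does not say which is meant, and a single baseline assessment cannot establish the order of cause.

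Third, the article does not say how the outcomes are made binary. If the endpoint were improvement from baseline, the baseline value would already be inside it and the percentages above would not apply, although leaving baseline out would not thereby become safe.

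Fourth, adjustment for a baseline measured with error reduces the confounding without removing it. That also stands.

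A reader might infer that baseline adjustment would sharpen the estimates by removing residual variance, as in a linear model. That does not carry over to the planned logistic regression, where the construct's standard error rises.

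**Conclusion.** The point holds as a risk built into the stated adjustment set. As written, the model cannot separate a construct's prognostic value from its association with severity at baseline, and the data needed to do so are already scheduled.

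The size is conditional: about 20% to 99% false declarations against about 5%, for n = 305, a median split and correlations from (0.2, 0.4) to (0.5, 0.6), none of which except n comes from the article. The 5% also assumes an error-free baseline measurement.

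A reader might go further and conclude that such constructs will be declared predictors, or that the sponsor has decided against baseline adjustment. The article supports neither: it reports no correlations, it does not expressly exclude the baseline outcome, and a construct unrelated to baseline severity is not affected.

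**What to change.** In the Analysis strategy, add the baseline value of the same outcome (FIQ, PVAS or pain threshold) as a continuous covariate in each one-year model. State that the construct coefficient is its prognostic value beyond measured baseline severity. Report the model without baseline alongside it, labelled as a descriptive estimate of total prediction.

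The cost is a line or two of wording, with no new data and no patient burden. Some associations will look smaller and their standard errors will be somewhat larger. Since adjustment for an imperfectly measured baseline is incomplete, the report should acknowledge that some confounding by severity may remain.
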